## Abstract

**Background:**

Despite the improvement in the care management, women cancer patients who are still in employment find themselves for the most part obliged to stop working while they are having treatment. Their return-to-work probability is impacted by numerous psychosocial factors. The objective is to describe the development and the content of an intervention aimed to facilitate the return to work of female breast cancer patients and in particular the women in the most precarious situations through early active individualised psychosocial support (APAPI).

**Methods:**

The intervention proposed is made up of 4 interviews with a psychologist at the hospital, distributed over the year according to the diagnosis and conducted on the same day as a conventional follow-up consultation, then a consultation with a specialist job retention physician. We expect, in the first instance, that this intervention will reduce the social inequalities of the return-to-work rate at 12 months. The EPICES score will enable the population to be broken down according to the level of social precariousness. The other expected results are the reduction of the social inequalities in the quality of the return to work at 18 and 24 months and the disparities between the individual and collective resources of the patients. This intervention is assessed in the context of a controlled and randomised multi-centre study. The patients eligible are women aged between 18 and 55 years with a unilateral breast cancer with local extension exclusively, having received surgery followed by adjuvant chemotherapy, in employment at the time of the diagnosis and dealt with by one of the 2 investigating centres.

**Discussion:**

It is essential to assess this type of intervention before envisaging its generalisation. The study set in place will enable us to measure the impact of this intervention aiming to facilitate the return to work of breast cancer patients, in particular for those who suffer from social fragility, compared with the standard care.

## Background

With approximately 53,000 estimated new breast cancer cases in 2011, breast cancer is top of the list of cancers affecting women in France. The improvement in the care therapy and earlier diagnosis are increasing the probability of curing cancer and the 5-year survival rate is above 80% between 15 and 64 years [1]. Even if breast cancer patients have a lower probability of having a job than women in the general population of the same age [2-4], breast cancer often affects working women. The direct consequences of the occurrence of the disease for most of them are the need to take sick leave and the consequent significant loss of earnings [5,6]. Whereas the duration of the sick leave for these women is longer than for those suffering from another type of cancer, the return-to-work rate is higher [7,8]. However, one year after the first surgery, a female breast cancer patient has almost 3 times as much risk of no longer working as a woman in the general population (23% *vs.* 9%) [4].

Return to work is a major issue and frequently affects the quality of life, the financial security, the restoring of a stable social environment and the feeling of normality [9,10]. According to the studies, the return-to-work rates 10 months after the diagnosis vary between 56% and 91% [7,11]. In addition to the factors linked to the treatment and the disease, return to work is impacted by certain psychosocial characteristics. Thus, having a poor level of education, working part-time or experiencing job-linked difficulties (e.g. poor support from colleagues, a big physical and/or psychological workload) accentuate the repercussions of the disease on job retention and their return to work [9,10]. This is why special attention must be paid to the role of the social inequalities in the occupational rehabilitation and reintegration of these women.

In order to mitigate these difficulties and reduce these social inequalities, Amir and Brocky [12] recommend the inclusion as early as possible by the cancer care teams of the return-to-work issue in the course of therapy. The improving of the communication between the various health players, in particular between the general practitioner (GP) and the occupational physician, is also an avenue for intervention to be developed in order to promote a return to work [13]. Several intervention studies concerning the inclusion of actions designed to facilitate return to work in the course of cancer care have been conducted in recent years. However, through a review of the literature, Tamminga *et al. *[3] come to the finding that most of these interventions do not aim in the first instance to improve the return to work, but rather the quality of life and/or the general physical and psychological functioning. Furthermore, these interventions have not for the most part been the subject of randomised trials with a control group, which limits the attribution of the return to work to the intervention [3,14].

Owing to the impact of the factors influencing the return to work, the resultant inequalities and the interventions already conducted, we propose an intervention designed to facilitate the occupational rehabilitation of female breast cancer patients. An early active individualised psychosocial support (APAPI) would enable, in our opinion, help to be provided for the patients facing the greatest social and psychological difficulties and so limit the consequences of their disease on their work and generally speaking improve their quality of life. The objective here is to describe 1) the development and the content of our intervention, 2) the methods used in order to compare the effect of the APAPI on the reduction of the social inequalities of a return to work compared with that of the conventional therapy.

## Methods/Design

### Development of the intervention

The development of our intervention is based at the same time on 1) the factors identified in the literature having a positive or a negative influence on the return to work, 2) the results of the previous intervention studies designed to promote the return to work of cancer patients, 3) the data reported by the « health-employment-information-services » (SEIS) platform of the Lille CHRU (University Hospital Centre), designed to prevent the occupational exclusion of current or previous cancer patients.

### Factors associated with the return to work

Many factors associated with the return to work have been identified in the literature. These various factors can be classified into 3 categories: the individual characteristics, the work-linked factors and the disease or treatment-linked factors.

As regards the individual characteristics, the studies highlight in a consensual way that young breast cancer patients with a higher education level and a high socio-economic level have a more favourable return-to-work prognosis [8-11,15,16]. At the psychological level, a person’s propensity to talk about her disease with her colleagues, to ask for or to receive help and perceive and receive social support from her colleagues and superiors [17,18] and the level of control perceived as high of the disease and the treatment in the workplace are factors linked positively with a return to work [19]. Benefiting from the support of her family and the health professionals, as well as taking care of her health and implementing coping strategies would also facilitate the return to work [20].

As regards the work-linked factors, being in full-time employment at the time of the diagnosis, having a bearable workload, manageable job requirements and a certain job satisfaction appear to be good return-to-work predictors [8,11,19,21,22]. An adjustment of the working conditions at the time of the return to work also helps in bringing the date of this forward [18]. Grunfeld *et al. *[23] also identify that positive representations on the part of the employers concerning the impact of the cancer and the treatment on the work play a role in this process.

Lastly, as regards the factors linked to the disease and the treatment in the return to work of breast cancer patients, Amir and Brocky [12] show that the absence of pain, fatigue, dyspnea, physical limitations, mental co-morbidity, a good previous physical level and good health self-assessment promote the return to work. Furthermore, not having had chemotherapy during the course of treatment also appears to be a factor promoting the return to work [11].

Of the aforementioned individual characteristics and work-linked factors, some reflect a socio-economic precariousness demonstrating the importance of the social inequalities of the return to work: thus low incomes, a greater physical workload and a lower level of education are factors of social inequalities in the return to work for cancer patients compared with their more qualified counterparts with a lower physical workload and better incomes [16,24-26]. Recent studies confirm the impact of social inequalities in rehabilitation programmes for cancer patients. Thus, the study undertaken by Pauwels et al. [27] shows that the younger breast cancer patients with low incomes are, the more they need information and consultations with a psychologist and this right from the onset of the treatment compared with older women with better incomes. As for Holm *et al. *[28] they report that women with a low level of education and low incomes, living on their own, display a greater need for physical, emotional and financial support than women with a higher level of education. The authors recommend moreover paying special attention to people from precarious socio-economic groups, in particular by developing interventions aimed at offsetting these inequalities.

### Results of previous intervention studies

Several reviews of the literature concerning the content of the job-related intervention studies of cancer patients have been conducted by various authors in order to build on the already existing interventions and produce recommendations regarding methods and practices. The review of the literature conducted by Hoving *and al*. [14] is mainly composed of intervention programmes designed to improve physical, psychological and social rehabilitation. Of the interventions included for their methodological qualities, the one performed by Maguire *et al*. [29] shows that the group of patients given the benefit of individual interviews of the « counselling » type by a nurse have a higher return-to-work rate (*n* = 32.76%) than the control group (*n* = 25.54%).

According to Verbeek and Spelten [30], interventions should pay greater attention to and include more information, support and counselling about work-related issues not only from the health professionals but also from the employers. Furthermore, Grunfeld *et al*. [23] recommend the setting in place of a dialogue between employees and employers, as well as adjustments at the workplace in order to meet the needs of the patients and thus enable a gradual return to work.

As for Tamminga *et al*. [3] they put the emphasis on two main return-to-work prognostic factors: self-assessment of work ability and the physical workload. They underline the fact that return-to-work enhancement has rarely been the main objective of a study. More frequently the content of the interventions comprises vocational training, encouragement, work-related counselling and work adjustments.

According to Tiedtke et al. [31], meetings with the family, social and professional environment delivering information about the disease and the treatment would back up the adjustments set in place for breast cancer patients and therefore influence the return to work. However, the communication between the various health professionals is not necessarily efficient and does not provide optimum return-to-work support for the patient [31]. More precisely, the review of the literature done by Boer *et al. *[32] shows that multi-disciplinary interventions have real implications for the improving of the return to work compared with the conventional care model and compared with the other types of intervention.

Tamminga *et al. *[33] continuing the intervention study done by Nieuwenhuijsen *et al. *[13] using a booklet of practical advice (« 10 steps of advice ») for the patient and the occupational physician, propose an intervention study protocol aimed to improve the patient’s return to work via a randomized controlled trial. The content of their intervention is composed of 1) 4 meetings with a nurse in order to start the occupational rehabilitation as early as possible 2) a meeting with the patient, the occupational physician and the line manager in order to draw up a return-to-work plan, and 3) correspondence between the GP and the occupational physician in order to improve communication.

### The « Health-Employment-Information-Services » telephone platform

The « Health-Employment-Information-Services » (SEIS) telephone platform was created in Lille in 2006 given the demand from patients suffering from cancer or chronic diseases, the return-to-work difficulties, the needs highlighted by the professionals, the patients’ ignorance of the many aid facilities in existence and the need to develop local support. The main purpose of this facility is to prevent the occupational exclusion of people suffering from all types of health problems. Nurses trained in listening techniques inform and help the callers with all the procedures of a socio-professional nature. What is involved above all is ensuring the consistency of the support practices between the various health players and anticipating the brakes or the difficulties encountered by the patients with regard to their return to work. When a person calls the platform, they can be given information immediately that is tailored to their situation (pathology, occupational status, health insurance scheme …). Individual contacts with the networks of occupational health, job retention and return to work professionals are also proposed. An individualised follow-up through the periodic calling back of the callers up to 6 months after their enquiry is provided. The SEIS nurses find through their work that both the return to work time and the return to work conditions could be improved if certain steps were taken earlier. This backs up what several studies demonstrate – that job retention or the return to work is conditioned by 1) the support from the work colleagues and superiors for employees, 2) contact between the patient and their company during the sick leave, 3) the anticipating of the pre-return to work examinations with the occupational physician (examinations that take place during the sick leave in order to assess the employee’s state of health and thus facilitate the return to work), 4) the psychological state of the cancer patients and the emotional charge built up by the experience of the disease and the treatment.

To our knowledge no interventions exist that aim more specifically to reduce the social inequalities of the return to work. In the light of these different observations, and taking inspiration from the various results obtained by the intervention studies on the issue of the return to work, in particular the recommendations of Tamminga *and al*. [3], we have formed the hypothesis that the return to work in general and the social inequalities in particular could be positively impacted by the specific support covered by our intervention.

The particular feature of our intervention is the special attention given to the reducing of the social inequalities of the return to work of breast cancer patients; it was therefore this aspect that was emphasised in the construction of our assessment protocol of the effectiveness of this intervention.

### Content of the intervention

These various findings and experiences thus led us to plan the content of our intervention as follows: 1) 4 interviews with a psychologist at the hospital, conducted during the standard course of treatment, on the same day as the conventional follow-up consultation; 2) linked up with a consultation with a specialist return-to-work physician.

### Meetings with the psychologist

Four one-hour interviews are scheduled throughout the course of treatment. These interviews are coupled with the necessary travel for the dispensing of the care and therapy, not generating therefore any additional travel for the patients. These interviews are based on the problem solving method [34].

The first interview is conducted at the start of the treatment, on the same day as the first chemotherapy session. Its purpose, through a semi-directive interview, is to identify the repercussions of the disease and the treatment on the patient’s job situation, clarify her needs and her expectations with regard to her job, and her wishes and difficulties with regard to this situation.

The second interview is conducted on the same day as the 6^th^ chemotherapy session. Its aim is to help the patient clarify the gap between the actual situation and the desired situation thanks to problem analysing techniques. The situations to be overcome are analysed with precision, as are the brakes and the resources thanks to an analysis of the psychological tests that the patient will have undergone during the pre-test (detailed below). This intervention positions these psychosocial tests both at the level of the overall assessment of the research project and at the level of the intervention itself as a tool helping the patients to become aware of their resources, difficulties and changes over the course of time. With the patient’s agreement, an area for work resulting from the questionnaires is chosen (social support, coping, attitude with regard to problems). The SEIS platform is presented as a practical tool that can be mobilised during this interview in order to anticipate the return-to-work strategies as early as possible.

The third interview is conducted during the final chemotherapy session. It invites the patient to invent new strategies for reducing the difficulties identified via problem-solving techniques. The psychologist helps the patient to develop her psychosocial skills, test out new behaviours and call upon the external resources available such as the SEIS platform in order to promote the return to work. Depending upon the problem to be solved, patients may be offered relaxation techniques, role playing, or contacts with local professionals.

Between the 3^rd^ and the 4^th^ interview, the patient is invited to choose new strategies she feels capable of implementing in order to test them out in a real situation. This step corresponds to the implementation of an action plan.

Finally, the fourth interview is conducted 3 months after the completion of the radiotherapy, at the same time as a post-radiotherapy follow-up consultation. Its purpose is to examine one by one the adaptation strategies that have been tested between sessions 3 and 4 in order to determine their advantages and drawbacks, the results obtained and the emotions felt. It is a question of strengthening the feeling of self-efficacy thanks to the objectives attained, pursuing the problem-solving learning process with the objectives that have not been attained, generalising the new effective adaptation strategies and rethinking the ineffective adaptation strategies.

### Meeting with the job retention specialist physician

Support from the psychologist is complemented, following the final interview, with a job retention/return to work consultation with a physician specialising in the return to work. To this end the patient is asked to come with her latest medical results to a medical consultation at the usual treatment site. The return-to-work specialist then drafts a summary, using as a basis to work from the medical file and the psychosocial support assessment, together with recommendations for a return-to-work plan. This summary is forwarded, via the patient, to her company’s occupational physician and her GP. The aim of this consultation is thus to facilitate the communication between the various players involved in the return to work of the patient and promote a multi-disciplinary analysis of the patient’s needs and expectations.

### Intervention assessment methods

In order to assess the effect of this early active individualised psychosocial support (APAPI) compared with the conventional treatment of the reduction of the social inequalities of the return to work at 12 months, we set in place a comparative, randomised, prospective and multicentre intervention study.

The secondary objectives were to assess the effect of this APAPI compared with the conventional treatment on the quality of the return to work at 18 and 24 months, and on the individual and collective resources of the patients such as the perceived social support, the coping strategies, the attitude to problems, anxiety and depression, the quality of life and the contacts with the SEIS platform. Lastly, a cost analysis of the benefit of this action is also planned.

The Committee of Protect People NORTHWEST III gave a favorable opinion for the study APAPI the September 8, 2012. The CPP reference for this study is: 2012-13.

### Participants

In order to carry out this study we opted for the population of women aged between 18 and 55 years with a unilateral breast cancer with local extension having been given surgery followed by adjuvant chemotherapy, with or without radiotherapy, in employment (salaried employees, trades people and the professions) at the time of the diagnosis and dealt with by one of the 2 investigating centres.

The criteria for non-inclusion are the presence of in situ lesions, cancer relapse, a metastatic cancer at the outset, a bilateral location. The patients with physical, psychic, psychiatric or cognitive disabilities preventing them from replying to the questionnaires and taking part in the interviews, and people having received prior treatment for a serious illness lasting at least 6 months (owing to another pathology) and people under wardship or guardianship are also not included in this study.

### Recruitment and investigating sites

In order to have the most representative population possible, the recruitment and the intervention are performed at two investigating centres in Nord-Pas-de-Calais, the Lille Centre Régional de Lutte contre le Cancer (Centre Oscar Lambret) and the Douai Centre d’Imagerie et de Cancérologie (Centre Léonard de Vinci).

The Centre Oscar Lambret is a Private Health Establishment of Collective Interest highly specialised in cancer research. It is associated with the Lille University Hospital Centre (CHRU) and is part of the group of Cancer Centres within the French Federation of Cancer Centres. By belonging to this group, the Centre Oscar Lambret provides an additional guarantee of quality and effectiveness to its cancer treatment, teaching and research actions at the service of the patient. The centre deals with 1,800 to 1,900 breast cancer patients per annum, i.e. 30 to 35% of the cases in the region.

The Centre d’imagerie et de cancérologie Léonard de Vinci is a private establishment associated with a medical group comprising radiology, radiotherapy, scanner and MRI centres.

The centre treats 1200 to 1300 new cancer cases every year (all locations taken together).

### Care and randomisation of patients

The standard care for breast cancer patients at each site is the same: following the cancer diagnosis, the medical files of the patients are examined at a multidisciplinary coordination meeting the purpose of which is to decide on the course of treatment to be given. Within a timescale of 1 to 2 weeks from the diagnosis, the patients are seen by an oncologist who explains to them what their course of medical treatment will consist of and whether or not this will involve chemotherapy. An appointment is then made for the following week with a nurse for a pre-chemotherapy consultation. During this interview lasting approximately 90 minutes, the nurse reviews with the patient what she has understood about the diagnosis and the treatment and her concerns and needs. The nurse can direct the patient to other professionals (psychologist, dietician, physiotherapist, welfare worker). The first chemotherapy session takes place approximately 1 month after this consultation.

The study is therefore proposed by the medical oncologist during the first care consultation to the patients fulfilling the inclusion criteria in the 2 investigating centres. After having explained the study to the patients with the information leaflet, those who accept sign a consent form. Next the patients will be randomised into two groups: 1) Group A: the « intervention » group which will have the benefit of the early active individualised psychosocial support in addition to the usual care. 2) Group B: the «standard care » group hereafter referred to as the “control group” which will follow the regular course of treatment without having the benefit of the psychosocial support as described above. This standard care already includes tools for identifying situations of great social distress enabling the patients to be directed to the regular social helpers.

Just after the inclusion, and before the start of their chemotherapy treatment, both groups of patients undergo the same battery of tests (pre-test).

They are then invited to do the same battery of tests and fill in the questionnaires again by letter 12 months after the start of their chemotherapy treatment. Follow-up of the return to work in terms of the rate and the conditions and a follow-up of the quality of life are also done at 18 and 24 months. In the event of their failure to reply to the questionnaires, the patients are re-contacted twice by telephone within the space of 15 days following the sending out of the questionnaires (Figure 1).

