### Questionnaires and psychological tests

During the pre- and post-tests (on the inclusion and 12 months after the diagnosis), for the two groups (A « intervention » and B « control »), we use a battery of tests with a questionnaire and validated psychological tests.

The questionnaire covers the socio-demographic characteristics of the patients, their disease (objective and subjective criteria such as fatigue, anxiety, mood disorders…), changes in their socio-professional situation during the study, as well as the difficulties they encounter with regard to the repercussions of their cancer on their situation (sick leave, financial aid, employment, recognition of disability, psychological aid, paramedical assistance and guidance). Social fragility is estimated using the Epices score [35], which will enable the women who are the most fragile socially speaking (FS+) to be distinguished from those who are less fragile socially (FS-) through a cut-off at the median. The Epices score was in fact built on a questionnaire comprising the various dimensions of precariousness: nationality, level of education, occupation, composition of household, housing, social protection, perceived health, income, leisure activities, financial difficulties, social integration, seeking healthcare, serious events experienced before the age of 18 years.

The measurement of the social support is done by the QSSP [36], the coping strategies of the patient by the WCC [37], the attitude to problems by the QAP [38], anxiety and depression by the HADS scale [39] and the quality of life by the FACT-G [40]. The quality of the return to work is estimated by the assessment of the work ability (WAI) [41].

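### The article places the Epices pre-test after randomisation and does not say it is completed before women learn their group; the FS+/FS- class should come from a pre-randomisation score

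*Protocol article*

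**What the plan says.** The section on care and randomisation of patients has the oncologist present the study and the woman sign consent. It continues: "Next the patients will be randomised into two groups". After describing the two groups it adds: "Just after the inclusion, and before the start of their chemotherapy treatment, both groups of patients undergo the same battery of tests (pre-test"). The section on questionnaires and psychological tests gives the timing a second time: "During the pre- and post-tests (on the inclusion and 12 months after the diagnosis), for the two groups". It does not place the pre-test relative to randomisation.

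The same section defines the subgroups. "Social fragility is estimated using the Epices score", and this allows the more fragile women (FS+) "to be distinguished from those who are less fragile socially (FS-) through a cut-off at the median". The dimensions listed for Epices include "housing, social protection, perceived health, income, leisure activities, financial difficulties, social integration, seeking healthcare", alongside nationality, education, occupation, household and events in childhood.

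Under statistical analyses, the primary comparison is the difference between groups A and B in the FS+ versus FS- gap in return-to-work rate. The battery is repeated later: "They are then invited to do the same battery of tests and fill in the questionnaires again by letter 12 months after the start". The article does not say outright which of the two administrations supplies the classifying score.

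**The concern.** Epices does more here than describe the population. It decides which of four cells each woman enters, and the primary estimate is a contrast of those four cells. Randomisation protects that contrast only if two things are independent of arm: how a woman is classified, and whether she is classified at all.

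If the pre-test follows allocation and women know their group, neither is assured. Interviews with a psychologist cannot be hidden from participants, and the article mentions no blinding. Some Epices dimensions are self-perceived and could be answered differently by a woman who has just been offered extra support than by one who has not. Group A women also have a reason of their own to think about their answers, because the second interview works from the pre-test psychological tests. A woman who withdraws on learning her group, before answering, has no FS class and drops out of the primary comparison. The 20% added to the sample size allows for lost numbers, not for loss that differs by arm.

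**Working it through.** **Order of events.**

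1. Care and randomisation of patients: consent, randomisation, then pre-test in both groups, before chemotherapy.
2. Questionnaires and psychological tests: pre-test at inclusion, for groups A and B.
3. Meetings with the psychologist: "The first interview is conducted at the start of the treatment, on the same day as the first chemotherapy session". The pre-test therefore precedes any contact with the intervention.
4. Time available, from the care section: the nurse consultation is in the week after the oncology consultation, and chemotherapy starts about one month after that. This leaves about five weeks.

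No section puts the pre-test before randomisation or says when allocation is disclosed.

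**The plan's own figures.** The sample size section gives an average return-to-work rate of 50% and a gap of 22 points, to be lowered to 8.5. The target is 22 − 8.5 = 13.5 points. With two equal halves (which a median cut implies), the rates are 50 + 11 = 61% in FS- and 50 − 11 = 39% in FS+. The stated 125 per group does not change with the order of the pre-test.

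**Sensitivity of the gap.** Assume no true effect and misclassification in one arm only. The error rates are assumptions; the article gives none.

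*Symmetric swap.* A fraction e of each half is placed in the other half:

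- Apparent FS- = 61(1 − e) + 39e; apparent FS+ = 39(1 − e) + 61e; gap = 22(1 − 2e).
- e = 5%: gap 22 × 0.90 = 19.8, shrinkage 2.2 points.
- e = 10%: 58.8 − 41.2 = 17.6, shrinkage 4.4 points.

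*One-directional shift.* A fraction f of FS- women is placed in FS+, and none the other way. If those moved have the average FS- rate, apparent FS- stays at 61 and apparent FS+ = (39 + 61f)/(1 + f):

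- f = 5%: (39 + 3.05)/1.05 = 40.05; gap 20.95, shrinkage 1.0 point.
- f = 10%: (39 + 6.1)/1.10 = 41.0; gap 20.0, shrinkage 2.0 points.

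*Women near the cut-off.* Both calculations give the moved women the average rate of their true class. If they instead have a rate near the overall 50%:

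- Symmetric swap: women with the same rate are exchanged, so the gap stays at 22.
- One-directional, f = 10%: FS- = (61 − 5)/0.90 = 62.2; FS+ = (39 + 5)/1.10 = 40.0; gap 22.2, practically unchanged.

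**Direction.** The primary contrast is gap in B minus gap in A. Shrinkage confined to A raises it and looks like a benefit. The same shrinkage confined to B lowers it and hides one.

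**The case against.** The strongest reply is that the article does not say what a reader might infer from it, namely that women already know their group when they complete Epices. No disclosure time is given. The pre-test is tied to inclusion, which may mean the signing of consent, and the reference to both groups may mean only that the battery is the same in each. The study design figure, which might show the order, is not available here. This stands: knowledge of allocation is an inference.

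It is equally tempting to call the subgroups post-randomisation in the damaging sense, as though treatment could have altered them. The documents do not support that either. The score is taken before the first interview, so what remains is differential reporting and differential loss. Much of Epices (nationality, education, household, housing, events before age 18) leaves little room for reporting to vary.

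The reply is also right that 4.4 points, about a third of the target, should not be read as the expected bias. Mood or expectation would more plausibly push answers one way, which halves the figure. Women whose class changes because of a small shift in answers lie near the median, which reduces it further. Placing the error in group A is a choice, since controls could misreport as easily. No arm-related withdrawal has been shown. Nor does the article say that the baseline psychological scores enter any comparison, so for those scales the point is one of good order only.

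What the reply does not remove is the written sequence. The classifier of the primary comparison is placed after randomisation, with no stated safeguard, in a trial whose participants cannot be blinded. Nor does the article state that the pre-test score defines FS. If the 12-month score were used, the classes would be formed after the intervention, which would be worse.

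**Conclusion.** The point holds as a weakness in the stated order, not as demonstrated bias. As written, the pre-test follows randomisation, nothing ensures that it precedes disclosure, and its Epices score is the natural (though unstated) source of the subgroups in the primary comparison.

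The size and direction are unknown. With 5% to 10% misclassification assumed in one arm only and rates of 61% and 39% in equal halves, that arm's gap shrinks by 1.0 to 2.0 points (one-directional) or 2.2 to 4.4 points (symmetric), against 13.5 sought. It could be close to nothing if only women near the cut-off move. Loss between allocation and pre-test cannot be sized from the article. The written order is certain; disclosure and magnitude are much less so. The change is worth making because it removes a risk to the primary comparison at little cost.

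**What to change.** For future inclusions, change the sequence to consent, pre-test (at least Epices and the baseline scores), then randomisation. State that FS+/FS- class comes only from this pre-randomisation score and that a single median cut-off, pooled over both arms, is applied. For women already included, report the number with missing Epices by arm.

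The sample size is unaffected. The cost is that women learn their group slightly later; about five weeks lie between the first oncology consultation and the first chemotherapy session, so the interval allows it. The article does not say where the pre-test is completed or how allocation is communicated, so the sites should confirm the practical arrangements.
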